### Study procedures — incremental TEACH audit and feedback intervention

In addition to the usual supervisor-led audit and feedback, sites randomized to the TEACH intervention will receive targeted C-SAT/SBT support from the centralized tele-critical care team. This will extend the local leader’s ability to promote increased adherence to C-SAT/SBT through direct messaging, education, and feedback. To support local ICU leaders during the initial education period, the tele-critical care nurse and respiratory therapist team members will develop educational materials and conduct trainings, including how to communicate with tele-critical care when they need assistance (see Table 2). See Additional File 7 for specific guidelines for daily tele-critical care operations in support of real-time audit and feedback for TEACH after the initial education period.

**Table 2 Tab2:** Strategies for deployment of the telehealth-enabled remote audit and feedback (TEACH intervention)

Domain	Organize clinical operations leadership team	Identify and prepare local site project team/site champions	Develop educational materials and conduct training	Facilitate relay of clinical data to clinicians in real time	Utilize remote monitoring and prompting to audit and deliver feedback
Actor(s)	Nurse and respiratory care leadership, tele-critical care nurse and respiratory care leadership, implementation advisors	Cross-disciplinary site teams including local site physician leader, nurse, and respiratory care project leads	Nurse and respiratory care leadership, tele-critical care nurse and respiratory care leadership, implementation advisor	Cross-disciplinary team including clinical and implementation effectiveness leadership, information technology	Tele-critical care nurses and respiratory therapists
Action(s)	Define standard workflow for the TEACH intervention Identify and address barriers to adherence	Identify and address local barriers to adherence to the TEACH intervention	Introduce TEACH intervention in staff meetings, provide individual training and reinforcement with nurses and respiratory therapists	Utilize an electronic dashboard that includes information on SAT/SBT performance along with electronic medical record and tracking data	Identify potential non-adherent patients, evaluate to confirm nonadherence, conduct outreach to bedside clinician, provide bedside consultation/facilitation, document interaction
Targets of the action	Local site project teams/champions	Front-line clinicians	Local site project teams/champions	Tele-critical care nurses and respiratory therapists	Front-line respiratory therapists and nurses
Temporality	Initiation through sustainment	Implementation through sustainment	Implementation phase	Initiation through sustainment	Implementation through sustainment
Dose	At least biweekly	Biweekly	At site deployment and periodic refresh as needed	Daily, real-time reporting	Daily, as needed
Implementation outcomes affected	Uptake, penetration	Uptake, penetration, fidelity	Uptake, penetration, fidelity	Uptake, penetration, fidelity	Uptake, penetration, fidelity

Interactions between the tele-critical care clinician and the bedside clinician are documented in the real-time electronic dashboard. Periodic reports on patterns in TEACH interactions and feedback from front-line clinicians are provided to local leaders of tele-supported sites. Local ICU leaders and champions will be coached to use this information to craft messaging, set goals, and make adjustments as needed with local bedside nurses and respiratory therapists.

### Data collection and analysis

We will collect patient data using customized clinical data entry workflows, queries of the Intermountain comprehensive electronic data warehouse, and structured manual chart review. Data on intervention acceptability will be collected via surveys implemented using the web-based Research Electronic Data Capture (REDCap) platform [53, 54].

### Primary exposure

The primary exposure will be the implementation strategy (usual audit and feedback alone [control] or supplemented by TEACH [intervention]) assigned to the study hospital where patient was located during their second intubated calendar day.

### Other independent variables

Patient demographics: Age, sex, race/ethnicity, relative socio-economic deprivation using a modified Singh area deprivation index [55, 56], insurance type, and comorbiditiesClinical data: Vital signs, respiratory failure etiology, APACHE IV score, laboratory results, medications (e.g., sedation and analgesic doses), and Richmond Agitation and Sedation ScaleVentilator data: Ventilator settings and contraindications for SAT/SBT

### Co-primary outcome (implementation)

The co-primary outcome for implementation is adherence to C-SAT/SBT (Table 3), calculated by dividing the number of adherent C-SAT/SBT days by the number of eligible patient days. An eligible patient day is defined as any day after the initial day of intubation and mechanical ventilation during which the patient remains intubated and receiving mechanical ventilation and does not meet any exclusion criteria.

**Table 3 Tab3:** Implementation and clinical effectiveness outcomes

Measurement category	Primary/secondary	Proctor implementation outcomes	Measure	Description
Implementation	Primary	Adoption	Clinician adherence to C-SAT/SBT	Percentage calculated by dividing the number of adherent C-SAT/SBT days documented by the number of eligible patient days
	Secondary	Feasibility	Incremental labor cost per patient days eligible for the TEACH intervention outreach	Incremental labor costs (base salary rate/fringe, supervisor overhead, overtime) divided by the number of patient days eligible for the TEACH intervention outreach
		Fidelity	Telehealth contact rate	Percentage calculated by dividing the number of successful contacts between the tele-critical care team and frontline nurses and RTs documented divided by the number of patient days eligible for the TEACH intervention outreach
		Acceptability	Clinician satisfaction scores	Percentage reporting agree or strongly agree on a 5-point Likert scale via a clinician survey
Clinical effectiveness	Primary	N/A	Patient ventilator free days to day 28	Number of days from the time of initiating unassisted breathing to day 28 after initiation of IMV, assuming survival for at least two consecutive calendar days after initiating unassisted breathing and continued unassisted breathing to day 28
	Secondary		Reintubation rate after intentional extubation	Proportion of patients undergoing intentional extubation who require reintubation for respiratory failure within 72 h. Excludes reintubations for < 24 h for the purpose of a surgical procedure
			Unintentional extubation incidence and reintubation rate	Separate from intentional extubation. Tracks unintentional extubations and rate of reintubation with 72 h
			Ventilator-associated pneumonia rate	New antibiotic administered in an intubated patient associated with a positive respiratory culture
			Richmond Agitation and Sedation Scale	Average Richmond Agitation and Sedation Scale each calendar day over the first 7 days from intubation. Recorded every 4 h by nursing
			CAM-ICU score	Identifies the presence or absence of delirium. Recorded every 12 h by nursing
			Delirium and coma-free days	Days free of delirium and coma to day 28. Delirium-free defined by the CAM-ICU score and coma-free defined by a RASS of > − 4
			Time to first ICU activity	Defined as a Johns Hopkins Highest Level of Mobility Scale of ≥ 2
			ICU length of stay	Duration of stay in the ICU in days
			Hospital length of stay	Duration of stay in the hospital in days
			Hospital discharge disposition	Home, skilled nursing facility, long-term acute care facility, or rehabilitation facility
			Mortality — hospital, 30-day and 90-day mortality	Raw unadjusted mortality and adjusted mortality as defined in the methods

A C-SAT/SBT adherent day is defined as an eligible patient day when the patient is both SAT adherent and SBT adherent (defined below). Additionally, if an SAT was passed, then at least one of the following criteria must be met: (1) the SBT event must also follow the SAT event and occur within 2 h, or (2) the SAT and SBT events must both occur before noon and contain charted evidence that the patient was responding to commands when the SBT event occurred.

An SAT adherent day is defined as an eligible patient day when charted evidence of any one or more of the following is documented: extubation, no sedation, SAT contraindication, successfully passed SAT, performed but failed SAT, or no SAT necessary (i.e., the patient is awake and responsive).

An SBT adherent day is defined as an eligible patient day when charted evidence of any one or more of the following is documented: extubation, SBT contraindication, documentation of spontaneous parameters, or performed SBT.

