### Secondary outcomes (implementation) 

Secondary implementation outcomes were categorized using Proctor’s measurement framework [47] and includes feasibility (incremental labor hours of the telehealth nurse and respiratory therapist roles), fidelity (contact frequency between telehealth roles and bedside clinical team), and acceptability (Table 3). To report acceptability, upon achieving stable adherence to the C-SAT/SBT, the research team will disseminate a survey tool using the secure REDCap data management system to capture front-line clinician impressions regarding acceptability of either study arms. The anticipated survey population will include approximately 150 ICU physicians and advanced practice clinicians (medical/surgical intensivists and hospitalists), 575 ICU nurses and nurse supervisors, and 250 respiratory therapists and respiratory care supervisors drawn from the 12 hospital sites. To measure acceptability, we will adapt the Acceptability of Intervention Measure (AIM), a previously validated 4-item measurement instrument, informed by the Unified Theory of the Acceptance and Use of Technology [57]. AIM measures approval, appeal, likability, and general willingness to accept the incremental telehealth-enabled audit and feedback implementation strategy versus supervisor-directed audit and feedback alone using an ordinal 5-point Likert scale. We have targeted a 40% response rate for analysis purposes, sufficient to capture important differences in attitudes across intervention and control participants and clinician roles.

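### Acceptability is collected as a four-item ordinal scale but reported in Table 3 as one percent-agree figure, which discards information, and the text leaves open which strategy clinicians rate

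*Protocol article*

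**What the plan says.** Acceptability is a secondary implementation outcome, described in two places in the Protocol article.

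- **Secondary outcomes (implementation)** names the instrument: "we will adapt the Acceptability of Intervention Measure (AIM), a previously validated 4-item measurement instrument". It is scored on an ordinal five-point Likert scale and covers approval, appeal, likability and willingness to accept.
- **The same section gives the object of the rating twice.** The survey is to "capture front-line clinician impressions regarding acceptability of either study arms". Two sentences later, the instrument is said to measure "general willingness to accept the incremental telehealth-enabled audit and feedback implementation strategy versus supervisor-directed audit and feedback alone".
- **The intended contrast** is between arms and between roles. A 40% response is called "sufficient to capture important differences in attitudes across intervention and control participants and clinician roles". The survey population is about 150 physicians and advanced practice clinicians, 575 nurses and nurse supervisors, and 250 respiratory therapists and respiratory care supervisors.
- **Table 3** (under Co-primary outcome (implementation)) labels the acceptability row as clinician satisfaction scores and defines it as "Percentage reporting agree or strongly agree on a 5-point Likert scale via a clinician survey".

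No effect size, power or test is stated for this outcome.

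**The concern.** There are two issues.

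**Form of the outcome.** Four ordinal items give each clinician a graded score. Table 3 replaces this with one proportion, cut between neutral and agree. That loses the distinction between agree and strongly agree, and all gradation below the cut. If the cut is applied to the respondent rather than to each item, it also loses the number of items endorsed. The table's label adds a small mismatch, because satisfaction is not among the constructs that the text lists.

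**Object of the rating.** A survey asking each clinician about the strategy in use at their own hospital gives a between-arm comparison of two strategies in use. A survey asking about TEACH as against supervisor-led feedback is a comparative preference. Clinicians at the six control hospitals could give that only for an add-on they were not assigned, and the between-arm difference would then not measure acceptability in use.

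The article's statement of contributions says that the trial will inform whether telehealth can be more acceptable to clinicians. Acceptability is the outcome that speaks to that claim.

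**Working it through.** The article states no figure for this outcome, so there is none to reproduce. What follows illustrates the cost of the summary chosen in Table 3.

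**Respondents (from the article).** 150 + 575 + 250 = 975. At the 40% target, 0.40 × 975 = 390. An equal split (assumed) gives 195 per arm.

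**Simulated answers (all inputs assumed).** Each clinician has four items generated from a one-factor latent normal with inter-item correlation 0.6 to 0.8. Items are cut into five categories at −1.5, −0.7, 0.1 and 1.1. The TEACH arm is shifted by 0.25 latent SD. There are 400,000 simulated clinicians per arm.

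**Level of the percentage.** The same control-arm answers give:

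| Scoring | Percent agree |
|---|---|
| At least one item | 65–73% |
| A single item | 46% |
| Mean of 4 or more | 28–31% |
| All four items | 20–28% |

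**Power.** With standardised effect *es* (difference in means divided by the SD of the score), *n* per arm and design effect *DE*, two-sided 0.05:

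power = Φ(es × √(n / (2·DE)) − 1.96)

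For n = 195, √(195/2) = 9.874 at DE = 1 and √(195/4) = 6.982 at DE = 2.

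| Score | es (approx.) | DE 1 | DE 1.5 | DE 2 | DE 3 |
|---|---|---|---|---|---|
| Respondent dichotomised (any item, all items, or mean ≥ 4) | 0.201–0.232 | 51–63% | 37–46% | 29–37% | 21–26% |
| Pooled percent agree (share of a clinician's items agreed) | 0.240–0.273 | 66–77% | 49–60% | 39–48% | 28–34% |
| Mean of four items (1–5) | 0.267–0.295 | 75–83% | 58–66% | 46–54% | 33–39% |

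Worked case, lower end of the mean score: 0.267 × 9.874 − 1.96 = 0.68 and Φ(0.68) = 75%. At DE = 2, 0.267 × 6.982 − 1.96 = −0.10 and Φ(−0.10) = 46%.

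The ranges in adjacent rows touch because each spans several correlations. At a fixed correlation and DE = 1, the mean is ahead of pooled percent agree by about 6 to 9 points and ahead of the respondent-level cuts by about 20 to 30. A repeat with another random seed gave figures within about two points of these, in the same order.

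**Object of the rating.** The phrase about either study arm, together with the planned contrast of intervention and control participants, fits each clinician rating the local strategy. The comparative phrase (TEACH versus supervisor-led feedback alone) fits a comparative question put to everyone. The two need different survey stems, and the section does not say which applies.

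**The case against.** The other side has several good points.

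- **No contradiction.** A reader might infer that text and table contradict each other. They do not. The text names an instrument and Table 3 names a summary of the same five-point scale, and the two can stand together.
- **The combining rule may sit elsewhere.** How four items become one percentage is a scoring detail that an article may leave to the full protocol or analysis plan. The plural in the table label would even fit item-by-item reporting. So the spread from 20–28% to 65–73% shows sensitivity to scoring and is not evidence of an omission.
- **Nothing says that control clinicians rate TEACH.** A reader might infer it from the comparative wording, but that phrase may simply describe the two strategies under study. Only the ambiguity can be asserted.
- **The efficiency loss depends on the reading.** If percent agree means the pooled share of items, the loss is 6 to 9 points and not 20 to 30. With clustering, the mean score itself has only moderate power.
- **Percent agree is easy to read**, and the article announces no hypothesis test for acceptability.

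All of this narrows the point. It does not remove it. Table 3 does fix a dichotomised outcome, the text does intend a between-arm comparison, and the mean loses less information under every scoring rule and design effect examined.

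**Conclusion.** The point holds as a minor improvement. Table 3 fixes a less informative summary than the survey will supply. On assumed inputs without clustering, the percent-agree forms have 51% to 77% power and the four-item mean 75% to 83%. Both fall with clustering and the order is unchanged. These figures rest on an assumed 0.25 SD shift, assumed correlations and cut-points, and an equal split of 390 respondents. They rank the summaries and do not predict the trial's power.

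Separately, the rated object is worded in two ways within one section. If the comparative wording governs the survey, control clinicians may be rating something they did not receive, and the between-arm difference would lose its meaning. The article does not settle which wording governs.

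The outcome is secondary. Neither co-primary analysis, the sample size nor the stopping rule depends on it.

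**What to change.** Before the survey is sent:

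1. In Secondary outcomes (implementation) and in Table 3, define acceptability as the mean of the four AIM items (1 to 5).
2. State that each clinician rates the audit-and-feedback strategy in use at their own hospital, and word the survey stem to match.
3. Compare arms with hospital clustering accounted for, for example by a linear mixed model with a hospital effect and clinician role.
4. Keep percent agree for each item as description.
5. Change the Table 3 label from satisfaction to acceptability (AIM).

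The cost is a survey stem and one table row, with no extra data. The drawback is a slightly less familiar headline figure, which the per-item percentages offset. If the survey has already gone out, the scoring can still be changed before the responses are analysed by arm. The stem cannot, so the report should then state what each arm was asked to rate.

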### Secondary outcomes (implementation) 

Secondary implementation outcomes were categorized using Proctor’s measurement framework [47] and includes feasibility (incremental labor hours of the telehealth nurse and respiratory therapist roles), fidelity (contact frequency between telehealth roles and bedside clinical team), and acceptability (Table 3). To report acceptability, upon achieving stable adherence to the C-SAT/SBT, the research team will disseminate a survey tool using the secure REDCap data management system to capture front-line clinician impressions regarding acceptability of either study arms. The anticipated survey population will include approximately 150 ICU physicians and advanced practice clinicians (medical/surgical intensivists and hospitalists), 575 ICU nurses and nurse supervisors, and 250 respiratory therapists and respiratory care supervisors drawn from the 12 hospital sites. To measure acceptability, we will adapt the Acceptability of Intervention Measure (AIM), a previously validated 4-item measurement instrument, informed by the Unified Theory of the Acceptance and Use of Technology [57]. AIM measures approval, appeal, likability, and general willingness to accept the incremental telehealth-enabled audit and feedback implementation strategy versus supervisor-directed audit and feedback alone using an ordinal 5-point Likert scale. We have targeted a 40% response rate for analysis purposes, sufficient to capture important differences in attitudes across intervention and control participants and clinician roles.

### Co-primary outcome (effectiveness)

The co-primary outcome for effectiveness will be patient-level ventilator-free days to day 28 (Table 3), defined as the number of days from the time of initiating unassisted breathing to day 28 after initiation of mechanical ventilation, assuming survival for at least two consecutive calendar days after initiating unassisted breathing and continued unassisted breathing to day 28 [51, 58]. If a patient returns to assisted breathing and subsequently achieves unassisted breathing to day 28, ventilator-free days will be counted from the end of the last period of assisted breathing to day 28. A period of assisted breathing lasting less than 24 h for the purpose of a surgical procedure will not count against the ventilator-free days calculation. If a patient was receiving assisted breathing at day 27, ventilator-free days will be zero; if the patient dies prior to day 28, ventilator-free days will be coded as − 1. Unassisted breathing is defined as follows: (1) extubated with face mask, nasal prong oxygen, or room air, (2) T-tube breathing, (3) tracheostomy mask breathing, (4) use of CPAP or noninvasive positive pressure ventilation solely for sleep apnea management, or (5) use of a high-flow oxygen system. For secondary effectiveness outcomes, see Table 3.

### Data management

Data management and analysis activities will occur via a collaboration between the Intermountain data management team and the University of Utah DCC. Under the subcontract agreement with the DCC and consistent with prior studies, the Intermountain study team is responsible for cleaning, aggregating, and exporting all data captured at the study sites and delivering to the University of Utah DCC for analysis via a secure server.

The DCC will present relevant study data and other trial issues to the DSMB, including the statistical trial design at the initial DSMB meeting, and the finalized trial statistical analysis plan at the end of the 6-month baseline measurement period prior to initiation of the clinical trial. The DCC will also perform two interim efficacy analyses (further described below) to consider early stopping for superiority if compelling evidence of a treatment effect is seen when comparing the two treatment arms. While the clinical trial is proceeding, the principal investigators will not have access to interim data regarding overall treatment efficacy by study arm.

### Primary quantitative analysis approaches

Reflecting the cluster-randomized design of TEACH, the primary analysis of treatment effect on adherence will use assigned treatment as a predictor in a logistic mixed-effects model with each observation of adherence as the outcome [59], with appropriate random effect terms including center, patient (nested within center), and calendar day (again nested within center) to model between-observation covariance. Models will also include each center’s baseline pre-C-SAT/SBT-implementation data available during the 6-month baseline period; this substantially improves power to detect a treatment effect, as baseline adherence substantially varies between hospitals. Treatment effect significance will be assessed using a one-sided Wald-type test with type I error of 0.05. To assess robustness of the primary analysis and provide a prespecified “backup” analytic approach if there are tractability issues, a model excluding calendar day effect, and a model fit using generalized estimating equations, are prespecified supportive analytic approaches.

The co-primary ventilator-free days outcome will have a highly skewed distribution, due to a high proportion of deaths, and appreciable proportions of surviving patients with 0 ventilator-free days, or ventilator-free days at or near the maximum possible value of 27. The primary analysis approach for the ventilator-free day outcome is effectively an adjusted rank-based analysis, implementing a proportional odds model including center as a random effect [60], including baseline as well as intervention ventilator-free days as outcomes, and adjusting for covariates including patient age, Charlson Comorbidity Index, PaO_2_/FiO_2_ ratio, and COVID-19 diagnosis [61]. Fitting this model for the ventilator-free day outcome at a granularity level achieving satisfactory convergence (selected in a prespecified fashion independent of treatment effect), a likelihood ratio test with type I error of 0.05 will assess significance of the TEACH intervention by comparing deviance of the model with three levels of treatment (baseline, control, and TEACH) to the corresponding model with treatment modeled as baseline versus intervention only.

